**Table 1. Planned questionnaire and sampling follow up**

| Time point (days)                           | Prior to or upon
inclusion | Daily whilst
admitted | 7 | 14 | 28 | 42 | 56 |
|---------------------------------------------|-------------------------------|--------------------------|---|----|----|----|----|
| Clinical records form A                     | X                             |                          |   |    |    |    |    |
| Clinical records form B/C                   |                               | X            | X | X  | X  | X  | X  |
| Sampling                             |                               |                          |   |    |    |    |    |
| CRP, WBC, Hb                                | X                             | X            |   |    | X  |    |    |
| Fasting blood-glucose                       |                               | X                        |   |    | X  |    |    |
| Immunological analyses                      |                               | X                        |   |    | X  |    |    |
| M. pneumoniae serology               | X                 |                          |   |    | X  |    |    |
| Nasopharyngeal sample for
multivirus PCR | X                 |                          |   |    |    |    |    |
| Upper airway sample             | X                             |                          |   |    | X  |    |    |
| Chest X-ray                                 | X                             |                          |   |    |    |    |    |

 CAP score will be obtained via telephone day 1-6 if the patient has been discharged

 Laboratory parameters will be taken daily until normalised

 *Mycoplasma pneumoniae* serology and upper airway sampling will be taken on day of inclusion

 Upper airway sample for diagnostic *M. pneumoniae* PCR and for subsequent phenotypic and genetic *M. pneumoniae* characterisation

Comorbidities: Will be obtained from the patient and medical records and recorded in clinical records form A. On the day of inclusion a nasopharyngeal aspirate will be taken for analyses of potential co-infection with Influenza A+ B, Parainfluenza 1, 2, 3, Human Bocavirus, Human Metapneumovirus, Coronavirus HKUL, OC43, 229E, NL63, Adenovirus, Enterovirus, Rhinovirus and Respiratory Syncytial virus.

### Laboratory Procedures

Analyses of CRP, WBC, Hb, PCRs and serologies will be done at respective hospitals affiliated Laboratory.

Upper airway samples for phenotypic and genotypic characterisation of *M. pneumoniae* will be stored in Universal Transport Medium and frozen at -80C at respective study site. Prior to analysis samples will be collected at irregular intervals and stored centrally at Karolinska Institutet biobank.

Fasting blood glucose values will be analysed on the wards whilst admitted.

Daily whilst admitted and at the day 28 follow up, 15 ml blood samples (10 ml EDTA tube and 5 ml tube without anticoagulants) will be obtained. The EDTA blood will be processed by ficoll centrifugation; obtained PBMC and plasma will be stored at liquid nitrogen and -70C respectively. The serum obtained from 5 ml blood (sampled without anticoagulant) will be stored at -70C.

Soluble factors such as cytokines and chemokines will be evaluated using immunoassays (LUMINEX, ELISA). Flow cytometry will be utilized to evaluate the cellular immune activation (T cells and monocytes). The cellular and soluble immune activation markers will be compared with clinical metadata to reveal the association with disease severity and clinical parameters.

### **Biobank**

Microbiological samples and blood samples will be stored as part of the Karolinska Institutet biobank.

### **Safety and adverse events**

Upon inclusion an entry will be made in the patient's medical record specifying that the subject is participating in this study, if betamethasone treatment is given, and that written informed consent is obtained.

### **Specification of safety parameters**

Safety parameters; Adverse drug reactions and serious adverse drug reactions and changes in vital signs.

Any apparent side effects experienced by the subject will be assessed from the time the subject signs the informed consent and as long as the subject is part of the study, and will be reported by study site personnel either as a Baseline Event or an AE. The study personnel will document any Baseline Events or AEs in the CRF, whether observed by the investigator or reported by the subject. The safety of the different treatment arms will be assessed with regard to AEs, baseline medical conditions, and findings from the physical examination and laboratory tests.

The Betamethasone dose used is expected to be well tolerated. Possible side effects include hyperglycemia, hypertension, gastric ulcers and mood changes such as confusion and agitation amongst others. For a full list of possible side effects from betamethasone treatment see the attached SmPC.

Possible adverse events will be elicited using a modification and Swedish translation (appendix 6) of Common Terminology Criteria for Adverse Events v4.0 (11) and they will be continuously reported to the sponsor. Adverse events related to betamethasone treatment shall be followed to assess reversibility.

An annual Development Safety Update Report (DSUR) will be sent to the Swedish Medical Products Agency and the Stockholm Regional Ethical Review Board.

### **Adverse event**

Definition: An AE in this study is defined as any untoward medical occurrence in a study subject. The occurrence does not necessarily need to have a causal relationship with the Investigational Medicinal Product (IMP). An AE can therefore be any unfavourable and unintended sign (including an abnormal laboratory finding), symptom, or disease temporally associated with the study, whether or not causally related to administration of the IMP.

The occurrence of an AE may come to the attention of study personnel during study visits and interviews of a study recipient presenting for medical care, or upon review by a study monitor who is scrutinising relevant source data.

Clarifications: Diagnostic and therapeutic non-invasive and invasive procedures, such as surgery, should not be reported as AEs. However, the medical condition for which the procedure was performed should be reported if it meets the definition of an AE. For example, an acute appendicitis that begins during the AE reporting period should be reported as “acute appendicitis” and the resulting appendectomy noticed under Comments. Pre-study conditions, which led to elective surgery during the time of the study, are not to be reported as AEs.

If an abnormal laboratory value or vital sign is associated with corresponding clinical signs and symptoms, the sign/symptom should be reported as the AE and the associated laboratory

result or vital sign should be considered additional information that is to be collected in the CRF.

### **Serious adverse event**

Definition: An SAE in this study is defined as any untoward medical occurrence that meets one of the following criteria:

- Results in death
- Is life threatening (the term “life threatening in the definition of “serious” refers to an event in which the subject was at risk of death and the time of the event; it does not refer to an event which hypothetically might have caused death if it was more severe)
- Requires inpatient hospitalization or prolongation of existing hospitalization
- Results in persistent or significant disability/incapacity
- Is an important medical event

### **Rating scales**

The investigator is to record all directly observed AEs and all AEs spontaneously reported by the subject in the subject’s medical records (source data) and in the CRFs using concise medical diagnostic terminology. All AEs must be graded for:

- seriousness
- intensity
- causality (possible relationship) to the IMP

The question asked will be “Have you had any health problems since your last evaluation?” If no AE has occurred during the period concerned, this should actively be noted in the CRF.

**Intensity:** The expression intensity of adverse events means the intensity of the event in the opinion of the subject. The intensity of each AE is to be graded by the Investigator.

**Causality:** The relationship between the IMP and each AE has to be classified by the Investigator using one of the following terms:

Unlikely: The onset of the AE and administration of the IMP are such that the medication is not likely to have any reasonable association with the AE.

Possible: It might be possible that the AE could have been caused by the IMP.

Probable: It is probable that the AE is caused by the IMP.

## **Reporting procedures for serious adverse events**

Events deemed as serious must be reported to the sponsor within 24 hours after the Investigator's awareness of the SAE. This short time frame is in compliance with international regulations. All SAEs should be reported by the site staff in the CRF.

If the initial report is not complete, it should be followed by submission of a more detailed report within five calendar days.

All SAEs must be followed until resolution or until the Investigator assesses them as being under full control.

The reporting period for SAEs starts at betamethasone administration and ends at the final follow-up visit 2 months after end of IMP administration.

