### **Study Procedures**

Randomisation: All participants will be randomised to either a treatment group or a control group (A or B) using [www.sealedenvelope.com](http://www.sealedenvelope.com). Randomisation is blocked (using random permuted blocks) with 1:1 allocation ratio to ensure that the groups are balanced periodically.

Treatment: All participants will take doxycycline (ATC J01AA02) 200 mg once daily until 10 days total effective treatment has been taken. If participants have been treated with active antibiotics before inclusion, treatment will be switched to doxycycline upon inclusion. Total effective antibiotic treatment duration will be 10 days. The doxycycline dose chosen is slightly higher than normal as the doxycycline minimal inhibitory concentration is very similar to that obtained when 100 mg is given daily. The treatment duration is ten days as this group of patients have complicated mycoplasma pneumonia.

Participants randomised to treatment with betamethasone will take 3 mg once daily days 1 and 2 and 2 mg once daily days 3, 4 and 5, given orally according to the SmPC.

Betamethasone intake will be observed whilst admitted and confirmed by questioning thereafter. After discharge, any remaining doses will be labelled with dose information as done in standard clinical practice and given to the patient to take at home.

The betamethasone dose has been selected based on clinical experience, similarity to that used for treatment of exacerbations of chronic obstructive pulmonary diseases and asthma, tolerability and likely acceptance by clinical practitioners.

Betamethasone (ATC H02AB01) is a corticosteroid with a Marketing Authorization in Sweden (MA number 6940). It will be provided free of charge to participants and taken from

the pharmaceutical store room of the ward. As the drug only is administered directly from the ward, no study specific marking - except dose to be taken - is needed.

Patients randomised to the control group will only receive standard care with doxycycline as described above.

Monitoring and follow up: Whilst admitted breathing rate, peripheral oxygen saturation (measured with pulse oximetry after 20 minutes of rest), oxygen use, pulse, blood pressure, body temperature, peak expiratory flow and mental state will be monitored three times daily and entered into computerised medical records.

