Medical records will be searched to determine values prior to inclusion in the study and data will be entered on to clinical records form B (appendix 2). Chest x-rays or CT scan will have been performed routinely prior to inclusion.

Following inclusion, participants will also be followed up with structured questionnaires (appendix 3, 4 and 5) to identify the community acquired pneumonia (CAP) score on days 1, 2, 3, 4, 5, 6, 7, 14, 28, 42 and at 2 months after inclusion. If the patient has been discharged, physiological parameters will not be recorded but the CAP score will be obtained per telephone. The CAP score is a disease-specific activity score for community acquired pneumonia; it ranges from 0 to 100, 0 marking the worst and 100 the best score (10).

Blood samples for analysis of C-reactive protein (CRP), white blood cell count (WBC) and haemoglobin (Hb) will be taken daily until normalised or discharge from hospital and on day 28. Fasting blood glucose and blood samples for immunological analyses will be taken daily until discharge and on day 28. Blood samples for *M. pneumoniae* serology will be taken on the day of inclusion and at day 28. A sample for diagnostic PCR and for subsequent phenotypic and genotypic characterisation of *M. pneumoniae* bacteria will be taken from upper airways prior to inclusion, upon inclusion and on day 28. Samples will be frozen at -80°C until phenotypic and genotypic characterisation. Patients will be discharged from the hospital at the discretion of treating physician. Follow up visits will be done on day 28 and by phone on days 42 and 56.

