## **Reporting period for adverse events**

All AEs, irrespective of nature, will be followed until resolution or until end of the follow-up period.

The reporting period for AEs starts at inclusion and ends at the final follow-up visit 2 months after inclusion.

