### **Insurance**

Participants are covered by "patientskadelagen" and the investigational medicinal product betamethasone is covered by "läkemedelsförsäkringen".

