### **Statistics**

Power calculation: Was done using [www.sealedenvelope.com](http://www.sealedenvelope.com). The significance level was set at 5% and the power at 90%. In the only randomised trial available, cortisone versus not cortisone resulted in defervescence by 48 hours in 100% and 0% respectively and hypoxemia lasted for a mean <2 versus >3 days, respectively. Our power calculation therefore assumes resolution of hypoxemia by 48 hours in 95% of participants with betamethasone and 65% of those without betamethasone. The sample size required in each group would then be 33. Assuming a 5% loss to follow up 70 patients need to be included.

Duration: Approximately one year for patient inclusion and follow up. The trial will end after the last visit of the last subject. A Declaration of End of Trial Notification will be sent to the MPA at the latest 90 days after the study has ended.

Data storage: All CRFs and signed informed consent forms will be collected from all study sites and stored in a locked cupboard in a locked room at Danderyd hospital for at least 10 years. Data will be double entered using EpiData 3.1 by the investigators at Danderyd Hospital. Study ID only will be used on computerised records. The key will be stored with the CRFs at Danderyd Hospital.

Data analysis: The data will be analysed using survival estimates of the primary endpoint. A per protocol and intention to treat analysis will be done. Loss to follow up will be censored at the time of loss to follow up. Final analysis will include a description of included participants, proportions of adverse events and any serious adverse events, the proportion of participants withdrawn or lost to follow up, the cumulative success and failure rates by week 8. Categorical variables will be compared using the  $\chi^2$  test or Fisher exact test and continuous variables using quantile regression.

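### The SAE reporting period is tied to betamethasone at both ends, so it is undefined for controls and conflicts with the AE period and the day 56 last contact

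*Protocol*

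**What the plan says.** Under Reporting procedures for serious adverse events, the protocol states: "The reporting period for SAEs starts at betamethasone administration and ends at the final follow-up visit 2 months after end of IMP administration". The same section requires a report to the sponsor within 24 hours of awareness, a fuller report within five calendar days if the first was incomplete, and follow-up until the event resolves or is judged to be under full control.

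Three other places bear on the window:

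- Reporting period for adverse events: "The reporting period for AEs starts at inclusion and ends at the final follow-up visit 2 months after inclusion". No arm is singled out.
- Specification of safety parameters: side effects "will be assessed from the time the subject signs the informed consent and as long as the subject is part of the study", and are reported either as baseline events or as AEs.
- Study Procedures (Monitoring and follow up): "Follow up visits will be done on day 28 and by phone on days 42 and 56". Table 1 also ends at day 56.

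On treatment, Study Procedures gives betamethasone as "3 mg once daily days 1 and 2 and 2 mg once daily days 3, 4 and 5" and says of the other arm: "Patients randomised to the control group will only receive standard care with doxycycline as described above". The Insurance section identifies the IMP in its statement that "the investigational medicinal product betamethasone is covered by" the drug insurance. Under Statistics, the final analysis is to include "proportions of adverse events and any serious adverse events".

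**The concern.** A reporting window needs a start and an end that can occur for every participant. Here the start is the first betamethasone dose and the end is counted from the last one. Neither event can happen in the control arm. An SAE is also an AE, so a single event falls under two rules with different start and end points.

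What is at stake is even handling of serious events. The trial is open-label, runs at fourteen hospitals and has no data safety and monitoring board. If sites resolve the gap for controls in different ways, the formal SAE process may be applied more consistently in the betamethasone arm. The SAE proportions in the final report could then rest on different windows in the two arms. All participants start as inpatients, and a prolonged hospital stay is itself one of the protocol's seriousness criteria, so relevant events are plausible in controls.

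**Working it through.** **Patients affected.** The protocol's sample size gives the denominator. With 95% and 65% resolved by 48 hours, 90% power, two-sided 5% (sidedness is not stated; two-sided reproduces the figure) and unpooled variance:

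n = (1.960 + 1.282)² × [0.95 × 0.05 + 0.65 × 0.35] / (0.95 − 0.65)² = 10.507 × 0.275 / 0.09 = 32.1, so 33 per group.

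66 / (1 − 0.05) = 69.5, so 70 in total. The stated figures reproduce. With 1:1 allocation, 70 / 2 = 35 patients are expected in the control arm.

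**Start and end of each period.** Assumptions: inclusion is day 1, the last betamethasone dose is on day 5, and two months is 56 to 61 days. The protocol itself uses two months and day 56 for the same last contact, which supports the lower value.

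| Period | Betamethasone arm | Control arm |
|---|---|---|
| SAE, as written | first dose to day 5 + 56 = 61, up to 5 + 61 = 66 | no start; no end date |
| AE, as written | inclusion to day 56–61 | inclusion to day 56–61 |
| Last scheduled contact | day 56 | day 56 |

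Three mismatches follow.

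1. *Controls.* The SAE period never opens. Treating doxycycline as an IMP would not rescue the sentence, because the start names betamethasone.
2. *Start, betamethasone arm.* A serious event after inclusion but before the first dose is inside the AE period and outside the SAE period. The protocol does not give the length of this interval; it is probably short.
3. *End, betamethasone arm.* The SAE period ends 61 − 56 = 5 to 66 − 56 = 10 days after the last scheduled contact. On either reading of two months it ends 5 days after the AE period (61 against 56, or 66 against 61). Both sections call their end point the final follow-up visit, but they date it from different events.

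The start in Specification of safety parameters (consent) is a third anchor. Study population has the consent form signed upon inclusion, so this difference may be small, but the wording still differs.

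**What still captures control events.** The Adverse event section defines an AE as any untoward occurrence in a study subject, related to the IMP or not. Rating scales requires all AEs to go into the CRF and be graded for seriousness. The SAE section sends all SAEs to the CRF without restriction by arm. Taken with the AE period, a serious event in a control should be recorded and graded serious from inclusion.

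**What remains undefined for controls.** The 24-hour report, the five-day detailed report, and follow-up to resolution or full control have no period in which they apply. AE follow-up is weaker, since it may stop at the end of the follow-up period.

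**Size of any effect.** The protocol gives no SAE rate, so no under-count can be computed. For scale only, at assumed rates of 2%, 5% and 10%, the expected number of control patients with an SAE is 35 × 0.02 = 0.7, 35 × 0.05 = 1.75 and 35 × 0.10 = 3.5. These are events whose formal handling would be unclear, not events lost. Each such patient, if classified differently, moves the control proportion by 1 / 35 = 2.9 percentage points.

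**The case against.** The strongest reply is that the protocol collects the data anyway. AEs are recorded in every participant from inclusion, every AE is graded for seriousness, and all SAEs go in the CRF. On that view, the faulty sentence affects only expedited notification to the sponsor. Most of this stands. A reader might infer that SAEs are captured in the betamethasone arm only, or that deterioration in controls goes unreported. The documents do not support either inference, given those rules. In addition, vital signs and oxygen use are monitored three times daily in all admitted participants, and time to discharge is a secondary endpoint.

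A reader might also infer that a planned between-arm SAE comparison is biased against betamethasone. That too goes further than the text. The Statistics section lists SAE proportions in a descriptive sentence and names no dedicated SAE test; only its general chi-square or Fisher sentence could cover one. Specification of safety parameters assesses the arms on AEs, whose window is the same in both. If controls were under-reported, the distortion would run against betamethasone, but nothing in the protocol shows that they would be.

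It can also be said that the 5 to 10 day overrun is loose wording, since the only final contact is on day 56 and reporting runs from awareness, not from scheduled contacts. This is a fair reading of intent, and the 10-day figure does need calendar months. But the sentence counts its end from the end of IMP administration, so it cannot be squared with day 56 as it stands.

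What the reply does not remove is the rule itself. Recording an AE is not the same as applying the SAE procedure, and for controls the stated period for that procedure does not exist.

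**Conclusion.** The SAE reporting period is wrong as written. It is undefined for about 35 of 70 patients, leaves out SAEs between inclusion and first dose in the betamethasone arm, and ends 5 to 10 days after the last scheduled contact (two months taken as 56 to 61 days, last dose on day 5). It conflicts with the AE period and with the consent-based start in Specification of safety parameters.

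The consequence is a risk of uneven SAE ascertainment between open-label arms and of SAE proportions that rest on different windows. Missing control data are not shown, and the direction and size of any distortion cannot be established from the protocol. The primary endpoint, sample size and efficacy analysis are untouched. This is an internal inconsistency that should be corrected, but it is not a flaw on which the validity of the trial depends.

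**What to change.** Replace the last sentence of Reporting procedures for serious adverse events with wording such as: for all participants in both arms, the SAE reporting period is identical to the AE reporting period and runs from inclusion to the final contact on day 56. State day 56 in the AE section as well, so that the two-month wording has one meaning. In Specification of safety parameters, say that events between consent and inclusion are recorded as baseline events, a category that section already uses.

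Inclusion is the better start because the AE period already uses it. Randomisation is also common to both arms but would add another start point that matches neither existing section.

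The cost is one replaced sentence, two small alignments and matching CRF instructions, with no added visits or patients. The change shortens the betamethasone-arm window, as literally written, by the 5 to 10 days in which no contact was scheduled.
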